##### Health behaviors environment, and quality of life

This comprehensive questionnaire includes items related to nutrition and physical activity behaviors; environmental and social factors; other health behaviors (e.g. smoking); and limitations of activities due to health [4, 5, 57–65]. In addition, physical activity and sedentary behaviors will be measured using the 7-item International Physical Activity Questionnaire [66] and fruit and vegetable intake will be measured using the National Cancer Institute’s Fruit and Vegetable Questionnaire [67].

##### Social support and self-efficacy

Social support and self-efficacy for physical activity and diet will be measured using adapted versions of the Sallis tools [68–72].

##### Depression anxiety, stress, and resilience

Depressive symptoms will be measured using the 8-item Patient Health Questionnaire (PHQ-8) [73]. The 7-item Generalized Anxiety Disorder scale (GAD-7) will be used to measure anxiety [74]. Stress will be measured using the 10-item Perceived Stress Scale (PSS) [75–77]. Resilience will be measured using the Brief Resilience Scale [78].

##### Eating behaviors

The 21-item Three Factor Eating Questionnaire (TFEQ-R21) will be used to measure three eating behaviors: cognitive restraint, uncontrolled eating, and emotional eating [79–83].

##### Demographic variables (baseline only)

Program leaders and all SHHC subjects will complete a questionnaire that includes basic demographic variables (e.g. age, race/ethnicity, education, income, household size). Questions will be derived from national surveys (e.g. U.S. Census).

#### Anthropometric and physiologic measures

Anthropometric and physiologic data, including blood draws, will be collected by Western Health Screening (WHS) in Montana and by locally trained staff affiliated with the healthcare system in New York, with logistical support from program leaders and the study team. Blood will be drawn by trained, experienced phlebotomists. Anthropometric, physiologic, and dermal measures will all be taken at baseline and outcome assessments. For anthropometric and physiologic data, weight, hip circumference, and waist circumference measurements will be taken at the midpoint assessment (12 weeks).

##### Anthropometric measures

These measures will include height, weight, BMI, body fat, bone density, hip circumference, waist circumference, and body composition. Freestanding height boards will be used for height measurements, and balanced scales will be used for weight calculations. The Omron HBF-306 will be used to measure body composition by electrical impendence. The Achilles Express and Insight will be used to measure bone density. A retractable Gulick tape measure will be used for hip and waist circumferences, rounded to the nearest 0.125 inch. Height, weight, and hip and waist circumferences will be measured in duplicate, unless specified criteria are not met for the two measurements. In that case, a third measurement will be taken. These anthropometric measurements are primary outcomes for the study.

##### Physiologic measures

These measures will include blood pressure, resting heart rate, and fasting blood draws to assess 12-hour fasting glucose, hemoglobin A1C, C-reactive protein, and lipid panel including direct LDL cholesterol, total cholesterol, HDL cholesterol, cholesterol/HDL ratio, and triglycerides [84].

##### Dermal measures

As an objective measure of fruit and vegetable intake, study staff will use a Pharmanex BioPhotonic Scanner at baseline and outcome assessments, which non-invasively measures carotenoid levels in skin tissues using Raman Spectroscopy [85].

#### Physical activity, diet, and functional fitness measures

Measures of physical activity, diet, and functional fitness are secondary outcomes of the study.

##### Physical activity

Objective measurement of physical activity will be obtained using the ActiGraph Model GT3XE accelerometers worn for seven days at baseline, midpoint (12 weeks), outcome (24 weeks), one year, and eighteen months.

##### Diet

Dietary and supplement/vitamin intake will be collected and analyzed using seven automated self-administered 24-hour dietary recalls (ASA-24) [86]. At least one weekend day recall will be collected and at least three weekday recalls will be collected at all study time points.

##### Functional fitness

The chair test, bicep (arm curl) test, and 2-minute step test will follow the Senior Fitness Test protocol and be completed at baseline, 12-week, outcome (24 weeks), six months, and eighteen months [87]. The chair test and arm curl test consist of counting stands and arm curls completed in 30 seconds [87]. The 2-minute step test evaluates the number of times stepped in two minutes [87].

#### Process evaluation

##### Leader and participant-level process evaluation

Leaders will complete questionnaires after each class session related to attendance, as well as program delivery and fidelity [88, 89], and for SHHC sites they will report on subjects’ participation in HEART Club meetings and related activities. All SHHC participants will be provided with a Fitbit, a wireless activity tracker worn on the wrist, to enhance self-monitoring; they will be asked to share their Fitbit data with the study and that data along with the participant logs will provide on-going reported and objectively measured physical activity data. Participants will also be asked to complete a civic engagement questionnaire designed to assess awareness of local resources and civic engagement participation (past and current). Civic engagement attitudes and behaviors will be measured using the Civic Engagement Scale [90]. The questionnaire will be administered to all subjects at baseline and post-intervention.

##### Economic evaluation

Standard economic evaluation methods will be used to compare the value of the resources used in the SHHC project to the health consequences. Information on salaries, wages and benefits; cost of facilities (office space and utilities); equipment, supplies, and travel; and staff training will be collected from program leaders. Information on time costs (participants’ time at hourly wage rate), travel costs, and time spent exercising and planning/preparing meals will be collected from participants.

### Randomization

The study statistician will determine randomization assignment based upon a matched RUCA and region classification such that, for paired towns, one will be randomized to SHHC and the other will be randomized to SHHW. Following baseline assessments, town randomization assignments will be revealed to program leaders and subjects.

### Data management and analytic plan

#### Sample size calculations

Based upon the most recent findings from the SWHH study [38], in which participants lost 2.1 kilograms (SD = 2.6) over twelve weeks, it was determined that a sample size of 34 people per group will allow us to detect an effect size of 0.690 with a 2-sided test and a power of 80 %, conservatively allowing for a standard deviation of 3. Given that the data are clustered within counties, we also assumed intra-class correlation of 0.025 (with clusters of 12 people) and 10 % attrition [88], yielding a sample size requirement of 48 people per group (96 total) to obtain 80 % power. This sample size will also allow us to have sufficient power to detect an effect size of 0.690 among secondary outcomes, such as blood pressure. For example, based on prior exercise intervention research with overweight and obese midlife and older women [91], an effect size of 0.690 would correspond to a 10 % difference in systolic blood pressure with a standard deviation of approximately 24.

#### Quantitative analysis

Data will be collected online or double-entered into SPSS Data Builder by trained research personnel when needed. Univariate descriptive statistics for all variables will be examined. Problematic cases with outliers will be investigated and possibly rectified. Descriptive statistics by treatment groups will be compiled and tabulated. Comparison between conditions will be completed using chi-square test (binary and categorical variables), *t*-test (continuous variables), or non-parametric Wilcoxon Signed-rank test (continuous variables unsuitable for *t*-test). Since the observations are clustered within communities, we will use multi-level linear regression models to examine the unadjusted and adjusted effects of the intervention on the primary outcome (change in body weight) and secondary outcomes [physiologic (e.g. blood pressure, lipids, c-reactive protein, hemoglobin A1C); anthropometric (e.g. waist circumference); behavioral (e.g. 7-day accelerometry); and psychosocial (e.g. quality of life)] parameters using *intent-to-treat analysis*. The community will be entered in the model as a random effect. Adjusted models will control for baseline values of the outcome, age, education level, marital status, smoking status, and other relevant covariates as fixed effects in addition to the treatment variable. Interactions between the treatment variable and other covariates will also be tested. Potential mediating effects of behavior, psychosocial, and community awareness/participation variables will be examined. In addition to the direct effect of the intervention on the primary outcome, the indirect effects of the intervention on anthropometric and physiologic outcomes through behavior, psychosocial, and community awareness/participation outcomes will be investigated. Multiple regression and/or structural equation modeling will be used to assess the contribution of various indirect and the direct effect of the intervention.

To address Aim 2, change variables for outcomes of interest (e.g. BMI) will be created by subtracting the measurement at 24 weeks from the corresponding baseline measure. A multilevel model will be used, as the observations are nested within communities. To account for the non-independence between observations from members of the same town, workplace, or household, a community and workplace/household ID will be entered in the model as a random effect. Intervention will be entered as a fixed independent variable. The model will control for baseline values of the outcome, age, education, marital status, smoking status, and other relevant covariates as fixed effects. Interaction terms will also be tested.

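### The simple between-arm comparisons name a paired test for unpaired women and ignore clustering by town; the outcome models are not affected (minor)

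*Protocol article*

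**What the plan says.** All of this is in the protocol article, mostly under Quantitative analysis.

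- The paragraph first announces tables by arm: "Descriptive statistics by treatment groups will be compiled and tabulated".
- The next sentence assigns tests by type of variable: "Comparison between conditions will be completed using chi-square test (binary and categorical variables"), then the t-test for continuous variables, then the "non-parametric Wilcoxon Signed-rank test" for continuous variables that do not suit the t-test. It names no variable, no time point and no allowance for clustering.
- The sentence after that turns to the intervention effect: "Since the observations are clustered within communities, we will use multi-level linear regression models to examine the unadjusted and adjusted effects of the intervention". It covers the primary outcome and the secondary outcomes, and adds: "The community will be entered in the model as a random effect".
- The following paragraph, on Aim 2, repeats the multilevel approach: "a community and workplace/household ID will be entered in the model as a random effect".
- Under Randomization, the unit is the town: "for paired towns, one will be randomized to SHHC and the other will be randomized to SHHW".
- Under Sample size calculations, the plan allows for an ICC of 0.025 with clusters of 12 people.

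**The concern.** There are two separate faults in one sentence.

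**The test does not fit the data.** The signed-rank test works on within-pair differences or on a single sample. A comparison of the two programs sets one group of women against another, and no woman is matched to a woman in the other arm. The counterpart of the t-test for two independent samples is the rank-sum (Mann-Whitney) test.

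**The tests treat women as independent.** Whole towns are allocated, and both the sample size section and the very next sentence accept that women in one town resemble each other. Chi-square and t-tests without adjustment then use standard errors that are too small and reject too often. Renaming the signed-rank test as rank-sum would not cure this.

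At stake are the p-values that come from these simple comparisons. The sentence is not limited to baseline. It is also the only one that gives a between-condition test for categorical variables, since the multilevel models are described as linear. Categorical post-intervention measures do exist: the Simple 7 components are graded poor, intermediate or ideal, and the score is planned at all post-intervention time points.

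**Working it through.** **Inputs.** From the article: 16 communities, 8 per arm, about 12 women each; ICC 0.025; 10% attrition; effect size 0.690; two-sided test; 80% power. Assumed: a 5% significance level, which the article does not state, and the ICCs other than 0.025.

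**Step 1: the plan's own figure.** A two-sample t-test with effect size 0.690, two-sided 5% and 80% power needs 33.96, so 34 per group, as stated. The design effect is 1 + (12 − 1) × 0.025 = 1.275. Then 34 × 1.275 = 43.35, and 43.35 / 0.9 = 48.2, against the stated 48. The figure reproduces, so the plan itself works with a design effect of 1.275 and is consistent with a 5% level.

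**Step 2: size of a test that ignores clustering.** The true two-sided size is approximately 2 × (1 − Φ(1.96 / √DE)), with DE = 1 + (m − 1) × ICC and m = 12.

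| ICC | DE | True size at nominal 5% |
|---|---|---|
| 0.01 (assumed) | 1.11 | 6.3% |
| 0.025 (plan) | 1.275 | 8.3% |
| 0.05 (assumed) | 1.55 | 11.5% |
| 0.10 (assumed) | 2.10 | 17.6% |

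After 10% attrition, m = 12 × 0.9 = 10.8. At ICC 0.025 this gives DE = 1 + 9.8 × 0.025 = 1.245 and a size of 7.9%.

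**Step 3: check by simulation.** With 8 towns of 12 women per arm, no true effect and ICC 0.025, the unclustered t-test rejected in 8.1% of 40,000 runs and the rank-sum test in 7.3% of 10,000 runs. A t-test on the town means rejected in 5.0%. The excess therefore comes from ignoring the towns, and an analysis of town summaries removes it.

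**Step 4: signed-rank on unpaired women.** With unequal arms there is no complete set of pairs and the test cannot be run. With equal arms the pairing is arbitrary. In one simulated data set (96 per arm, true shift 0.25 SD, no clustering), 2,000 random pairings gave p-values from 0.04 to 0.66 (5th to 95th percentile 0.12 to 0.37); rank-sum gave 0.23. In 4,000 simulated data sets with no effect and no clustering, the signed-rank test on arbitrary pairs rejected 4.7% of the time. So the fault here is not excess rejection: the result depends on row order.

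**The case against.** A reader might infer from the sentence that the trial's comparisons between arms in general rest on these tests, and hence that its main results are invalid. The article does not support that. The next sentence assigns even the unadjusted effects on the primary and secondary outcomes to a multilevel model with a community random effect, and the Aim 2 paragraph repeats this. The sentence on simple tests follows the one on tabulating descriptive statistics, so a p-value column in a descriptive or baseline table is the most plausible use. This objection stands, and it limits the point to those comparisons.

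Other points on that side:

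- **A naming slip.** Probably so, and with unequal arms it would show itself at the first run. That limits the harm, but the named test is still wrong. A signed-rank test on differences between paired towns would be legitimate; however, the sentence chooses tests by variable type and mentions no town summaries.
- **Pair-matching.** The size formula treats towns as unmatched. If matching on RUCA and region removes between-town variance, the excess is smaller. This stands as a caveat.
- **Detail left to a fuller document.** Which variables are tested may well be set out elsewhere. The point does not depend on that omission, because the wrong test is stated in the article itself.

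One could also argue that inflated baseline p-values would steer the choice of the further covariates that the adjusted models leave open. The article does not say how those are chosen, so this remains conjecture.

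**Conclusion.** The point holds for the simple comparisons between conditions and no further. The signed-rank test is the wrong test for two arms of unpaired women. The chi-square and t-tests as written ignore the randomized towns. At the plan's ICC of 0.025, an unclustered two-sample test would run at about 8% instead of 5%. That rests on an assumed 5% level, 12 women per town and no gain from matching; the range of about 6% to 18% rests on assumed ICCs.

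The analyses of body weight and of the secondary outcomes assigned to the multilevel linear models are not touched. What remains open is a categorical post-intervention measure, for which chi-square is the only test named. Severity: minor.

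**What to change.** 1. Replace the signed-rank test with a two-sample method, such as the rank-sum test.
2. Either present the simple comparisons as descriptive, without p-values, or use versions that respect the towns: a linear or logistic model with a community random effect, or a test on community summaries. Apply the same to any categorical post-intervention outcome.
3. State that inference on outcomes comes only from the multilevel models.

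The cost is a few words and trivial programming. Design, data collection and sample size do not change.

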#### Economic analysis

Standard economic evaluation methods will be used to compare the value of the resources used in the SHHC project to the health consequences. As a first step, a cost analysis to identify and measure the direct, tangible costs of the resources used in program administration and implementation will be conducted. Important cost categories are salaries, wages, and benefits; facilities (office space and utilities); equipment, supplies, travel, and staff training. The cost analysis will be conducted from the narrow program perspective and from the broad societal perspective. For the program perspective, the focus will be on costs directly incurred by the agencies that administer and implement the program. These costs will include both direct payments and the value of in-kind contributions, such as the value of contributed office space. The results of the program-perspective cost analysis will provide information to judge whether and where the SHHC can be disseminated. For this purpose, it will be important to distinguish the costs of different components of the SHHC, for example, the costs of SHHC program development as distinct from the costs of the SHHC intervention. The detailed results will allow groups considering dissemination to develop cost predictions tailored to their specific context.

A preliminary cost-effectiveness analysis (CEA) of the SHHC intervention will be conducted. The CEA will build on the cost analysis conducted from the broad societal perspective. From the societal perspective, costs include not only the costs included in the program-perspective cost analysis, but also the opportunity cost of all resources used as a result of the intervention. Costs to participants are an important cost of the opportunity costs included from the societal perspective. Participants give up time that could have been used in other valued ways such as labor market work, household work, or leisure activities. Standard practice of measuring the value of participants’ time based on the relevant wage rates will be followed. The incremental costs of the SHHC intervention will be compared to the incremental effectiveness estimated from the controlled trial. The incremental cost-effectiveness ratio (ICER) will be calculated by dividing the incremental costs of the intervention by the incremental effectiveness. The calculated ICER in terms of the primary outcome will provide an estimate of the costs per unit change in body weight. This ICER allows the direct comparison of the cost-effectiveness of the SHHC intervention to alternative approaches to reduce body weight. The ICER will also be calculated in terms of standardized health outcomes including life years and quality-adjusted life years (QALYs). Epidemiologic models will be used to map the effects measured in the controlled trial (body weight, physiologic measures) to predict impact on life years and QALYs. The calculated ICER in terms of QALYS will allow the cost-effectiveness of the SHHC to be compared to a wide range of other health interventions for which QALY-based CEAs have been performed. An important goal of the preliminary CEA is to demonstrate feasibility and identify important issues to be addressed in more complete economic analyses.

## Discussion

There are notable disparities in risk for obesity, hypertension, diabetes, and CVD for people living in rural settings, particularly underserved rural areas. These disparities are driven by complex factors such as socioeconomic disadvantage, geographical distances/barriers, social and cultural issues, and limited access to healthcare, healthy foods, and/or physical activity opportunities due to environmental constraints, affordability, and availability. Moving beyond individual-level programs toward integrated, multi-level, community-engaged approaches may more effectively reduce rural CVD health disparities.

The novel integration of a multi-level, community-informed program combined with civic engagement and capacity building focused on local resource awareness and enhancement has the potential to effect clinically meaningful improvements among participants, as well as their families, friends, and communities. This innovative approach will also help sustain positive changes by linking behavior, social support, and the community environment. If successful, SHHC could be nationally disseminated, providing a feasible model for underserved rural communities across the nation to improve health, well-being, and quality of life and reduce CVD and other chronic diseases.

## Abbreviations

ACSM: American College of Sports Medicine
ALB: Albumin
ALT: Alanine aminotransferase
AST: Aspartate aminotransferase
ASA-24: Automated Self-administered 24-hour Recall
BMI: Body mass index
BUN: Blood urea nitrogen
CEA: Cost-effectiveness analysis
CVD: Cardiovascular disease
DASH: Dietary approaches to stop hypertension
EDTA: Ethylenediaminetetraacetic acid
GAD-7: Generalized anxiety disorder screener
GGT: Gamma-glutamyltransferase
HBEQ: Health behavior and environment questionnaire
HDL: High-density lipoprotein
IBC: Iron binding capacity
ICER: Incremental cost-effectiveness ratio
IRB: Internal review board
LDH: Lactate dehydrogenase
LDL: Low-density lipoprotein
MUA: Medically underserved area
MUP: Medically underserved population
PAR: Physical activity recall
PHQ-8: Patient health questionnaire depression scale
QALY: Quality adjusted life years
RUCA: Rural urban continuum code
SHHC: Strong hearts, healthy communities
SWCC: StrongWomen change club
SHHW: Strong hearts, healthy women
SWHH: StrongWomen healthy hearts
SPSS: Statistical package for the social sciences
SWST: StrongWomen strength training
TFEQ-R21: Three factor eating questionnaire
TSH: Thyroid stimulating hormone
WHS: Western health screening
